### Data monitoring

Since all outcomes are collected online, the risk of data loss or corruption is minimal. The data are stored encrypted and are only accessible by the people running the study. The collection and storage of data will adhere to the Swedish Personal Data Act.^54^ This study will not have a formal Data Monitoring Committee and no interim analysis will be performed. Previous studies and clinical experience indicate minimal risk for the participants. Moreover, participants will be asked about any adverse events experienced during the study period.

### Planned missingness design

The study will utilise a planned missingness design for the weekly measures.^55^ This is to decrease the number of items each participant must answer each week, but still retain a good temporal resolution. Each participant will be randomised to one of two measurement schemes. This design effectively leads to biweekly measures for Inventory of Consequences Scale for the Gambler and CSO (ICS) and weekly measures for PHQ-9, GAD-7, RAS and TLFB. Table 3 outlines the two variants.

**Table 3 BMJOPEN2015008724TB3:** Planned missingness design for the weekly measurements, participants are randomly assigned to one of two measurement schemes

	Days from randomisation								
	0	7	14	21	28	35	42	49	56
Scheme 1	X	O	O	O	X	O	O	O	X
Scheme 2	X	O	X	O	O	O	X	O	O

X=ICS only; O=PHQ-9, GAD-7, RAS and TLFB (last 7 days).

GAD-7, Generalised Anxiety Disorder Scale; ICS, Inventory of Consequences Scale for the Gambler and CSO; PHQ-9, Patient Health Questionnaire-9; RAS, Relationship Assessment Scale; TLFB, Timeline followback method.

### Process measures

To better understand what mechanisms mediate change during the study, data on treatment involvement will be collected, in addition to the weekly measures. Treatment involvement will be measured as data completion, time spent with the treatment site and the number of page views on the site, and will be collected unobtrusively as participants visit the treatment site.

### Planned subgroup contrasts

It is hypothesised that the following factors will predict treatment response: (1) type of relationship with the IP (parent, romantic partner or other) and (2) if the CSO lives with the IP.

### Randomization

CSOs will be randomised to one of the two treatment arms (1:1 ratio) after eligibility and pretest assessment is completed. The allocation sequence will be generated by a computer random number generator. To ensure balanced groups, block randomisation will be used. Each block's size will be randomly chosen from the set (4, 6, 8), and be unknown to the researchers involved in the study. A research assistant who is independent from the study will perform the treatment allocation, using sealed, sequentially numbered, opaque envelopes.

### Statistical analyses

Owing to the hierarchical structure of the data and the planned missingness design, analyses will be performed within the linear mixed models framework, such as to model the variability and dependency at the different levels. Treatment entry rates will be analysed using discrete-time event history models (ie, survival analysis).^56^ Survival analysis enables the evaluation of *whether* and *when* events occur; this will be used to compare time to treatment entry and differences in treatment entry rates in the study. Continuous outcomes will be analysed using a linear mixed models approach.^57^ Model building will follow the data-driven and theoretical approach described in Singer and Willet.^56^ Time will be split into two periods by a piecewise linear function^58^; this makes it possible to parsimoniously model change during treatment and follow-up data. Additionally, we hypothesise that treatment engagement will be associated with a reduction on the ICS self-report, and will test this hypothesis by joint modelling.^59^ Furthermore, for the analysis of the timeline followback reports (count data), it is anticipated that the data will be positively skewed and bounded at zero. Hence, generalised linear mixed models will be fitted, specifically zero-inflated Poisson models. In the case of overdispersion, zero-inflated negative binomial regression models will be fit.^60^

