### Blinding

Neither participants nor counsellors will be blinded to treatment allocation. Baseline assessment occurs prior to randomisation, and follow-up assessment will be self-reported via the internet.

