#### Sample size

The study's sample size is based on power calculations for the primary outcome (ICS). Since no good parameter estimates are available for this study, standardised coefficients are used. Power is estimated for the primary between-groups comparison directly post-treatment. A linear mixed model with random intercept and slopes is assumed. First, it is assumed that the between-groups standardised mean difference (Cohen's d) will be at least 0.5 at post-test, standardised using the SD at baseline. Moreover, the individual heterogeneity in change is likely to be large. Therefore, individual change at post-treatment is estimated to have an SD of 0.8 around the standardised average estimate (ie, variance due to random slopes). This amount of heterogeneity means that the 95% prediction interval for individual treatment response is expected to vary between ±1.6 around the average change. Assuming a standardised within groups difference of 1, these estimated numbers imply that about 10% of the participants will be unimproved or have negative outcomes (given by the cumulative distribution function of the Gaussian distribution). Moreover, at post-treatment, we estimate that 75% of the variance will be between participants and a 25% residual variance. A shift in this ratio towards more residual variance will decrease power. Given these estimates, 75 participants are needed per group to achieve approximately 80% power, with α=0.05 (this power calculation used equation 2 in Ard and Edland^64^).

Moreover, on the basis of the treatment entry numbers reported in previous studies,^20^
^29^ it is estimated that the treatment entry rate for the wait-list group will be 15%. Thus, using formulas to calculate power for a test of two independent proportions,^65^ it is estimated that 75 CSOs per group will achieve 80% power (α=0.05) if the treatment entry rate in the CBT-CSO group is 35%. In this scenario, the power for a test of two proportions and the power for a survival analysis are essentially the same. Hence, power is not reported for a survival analysis.

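### Data-driven model building is not ruled out for the primary ICS test, and the estimator of the named post-test comparison and the use of the pre-randomisation baseline are left open

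*Protocol article*

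**What the plan says.** In the protocol article, Statistical analyses sends all continuous outcomes to linear mixed models and adds "Model building will follow the data-driven and theoretical approach" of a cited textbook. It fixes time as a piecewise linear function with two periods, treatment and follow-up. It does not exempt ICS from the model-building rule.

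Sample size is more specific. "A linear mixed model with random intercept and slopes is assumed", and "Power is estimated for the primary between-groups comparison directly post-treatment". The effect is a standardised mean difference that "will be at least 0.5 at post-test, standardised using the SD at baseline". For heterogeneity, "individual change at post-treatment is estimated to have an SD of 0.8" around the average. For the variance split, "at post-treatment, we estimate that 75% of the variance will be between participants and a 25% residual variance". The result is 75 per group for about 80% power at α=0.05.

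On timing, Blinding states "Baseline assessment occurs prior to randomisation", and Randomization likewise places allocation after the pretest. No section says how baseline ICS enters the analysis.

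**The concern.** A primary test should be one named parameter of one named model. Here the power calculation assumes a model, while the analysis section gives a building rule that covers the primary outcome too. Within a random intercept and slope model, a comparison at post-test can be estimated in three ways:

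- the model-based mean difference at post-test, with each arm having its own baseline mean;
- the difference in change (slope) between arms, again with free baselines;
- the post-test difference with the arms constrained to one baseline mean (or, nearly the same, with baseline ICS as covariate).

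All three target the same effect under randomisation, but their precision differs. Which of the first two is more precise depends on the intercept-slope correlation, which the protocol does not give and which becomes visible only in the trial data. Because baseline precedes randomisation, the arm means there are equal in expectation, so the third estimator is justified by design. At stake are precision and a primary result that does not depend on a choice made late, in a trial with unblinded participants who report their own outcomes.

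**Working it through.** **Inputs.** From Sample size: difference 0.5, slope variance 0.8² = 0.64 at post-test, a 75/25 variance split, 75 per arm, α=0.05. From Table 3: ICS on days 0, 28, 56 (scheme 1) or 0, 14, 42 (scheme 2). Assumed: two-sided test; post-test ICS at day 70; day 0 taken as the pre-randomisation value; half of each arm per scheme; no dropout; time scaled so that day 70 is 1.

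The 75/25 split allows several readings:

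- baseline variance 1, split as intercept 0.75 and residual 0.25;
- the split applied at post-treatment, as worded: total 1 + 0.64 = 1.64, residual 0.25 × 1.64 = 0.41, intercept 1 − 0.41 = 0.59;
- intercept 1 and residual 1/3.

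**The plan's own figure.** The cited equation is not at hand, so the standard random-slope form is used: variance of the slope difference = (2/n)[0.64 + σ²/Σ(t − t̄)²], where σ² is the residual variance.

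- Residual 0.25, pre and post only: Σ(t − t̄)² = 0.5, bracket 0.64 + 0.50 = 1.14. Then n = 2(1.960 + 0.842)² × 1.14/0.25 = 71.6, so 72. At 75 per arm, SE = √(2 × 1.14/75) = 0.174 and power = Φ(0.5/0.174 − 1.96) = 81.8%.
- Residual 1/3, four occasions: Σ(t − t̄)² = 0.59, bracket 0.64 + 0.565 = 1.205, n = 76, power at 75 = 79.7%.

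Both agree with the stated figure of about 80%, so that figure behaves like power for a difference in change.

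**The three estimators by hand, pre and post only, 0.75/0.25, zero correlation.** Variance × n/2, then power at 75 per arm:

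- post-test difference, free baselines: 0.75 + 0.64 + 0.25 = 1.64, 66.7%;
- difference in change: 0.64 + 2 × 0.25 = 1.14, 81.8%;
- common baseline: 1.64 − 0.75² = 1.078, 83.9%.

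**With the Table 3 schemes plus day 70.** For each scheme the covariance is V = ZGZ′ + σ²I, where G holds the intercept and slope variances and their covariance. The information X′V⁻¹X is summed over schemes and arms and inverted. Power = Φ(0.5/SE − 1.96). At zero correlation:

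| Intercept / residual | Post-test, free | Change, free | Common baseline |
|---|---|---|---|
| 0.75 / 0.25 | 68.9% (SE 0.204) | 84.4% (0.168) | 86.0% (0.165) |
| 0.59 / 0.41 | 70.3% (0.201) | 75.5% (0.189) | 80.0% (0.179) |
| 1 / 0.33 | 61.1% (0.223) | 79.7% (0.179) | 81.8% (0.174) |

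**Varying the correlation**, with the variances held fixed:

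| Intercept / residual | Correlation | Post-test, free | Change, free | Common baseline |
|---|---|---|---|---|
| 0.75 / 0.25 | −0.5 | 90.8% | 84.4% | 94.9% |
| 0.75 / 0.25 | −0.3 | 81.7% | 84.4% | 90.6% |
| 0.75 / 0.25 | +0.3 | 58.7% | 84.4% | 84.4% |
| 0.59 / 0.41 | −0.3 | 81.9% | 75.6% | 86.2% |
| 1 / 0.33 | +0.3 | 51.6% | 79.7% | 79.7% |

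Across all 12 settings (three variance readings, correlations −0.5, −0.3, 0 and +0.3), the common baseline gained 0 to 16 points over the difference in change and 2 to 28 points over the free-baseline post-test difference. It was never less powerful than either. The order of the two free-baseline contrasts reversed within this range.

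**Data-driven building itself.** In 4000 simulated null trials, choosing among linear, log, quadratic and knotted time by AIC left the type I error near 5%. It reached 6.6% only if a significant result under any of the four shapes counted.

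**The case against.** Much of the primary comparison is fixed: outcome, timepoint, between-arm contrast, random effects assumed for power, and piecewise time. A reader might infer that the plan names no primary contrast, or that it will be picked after the data are seen. The text supports neither reading; only the estimator is open.

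A reader might also infer that the trial is underpowered, from the 69% figure. That does not follow. The 69% belongs to an estimator that the stated 80% does not appear to describe, and it needs a zero correlation and the 75/25 split moved to baseline. At a correlation of −0.3 the same estimator reaches about 82% with either 0.75/0.25 or 0.59/0.41. Against a difference in change, the common baseline gains only about 2 to 4.5 points at zero correlation.

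Third, a reader might blame the power spread on data-driven building, or expect it to inflate false positives. The spread comes from the choice of estimator within one fixed model, and the simulation showed no material inflation from choosing the time shape.

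Finally, baseline handling is often settled in an analysis plan, and this is a condensed article. That stands against treating silence on baseline as an error in its own right. It does not answer the sentence on model building, which is a stated rule that includes the primary outcome and sits beside a power calculation for one particular model.

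**Conclusion.** The point holds in a limited form. The model-building rule should not cover the primary ICS test, and the named post-test comparison should be tied to one estimator that uses the pre-randomisation baseline. At zero intercept-slope correlation the three candidates have power 69%, 84% and 86% (0.75/0.25), or 70%, 75.5% and 80% (0.59/0.41). For correlations from −0.5 to +0.3 and the three variance readings, the free-baseline post-test difference runs from about 52% to 91%.

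These figures rest on a day-70 post-test, no dropout, a two-sided test and a correlation that the protocol does not state. The preference for a common baseline does not depend on the reading: it was at least as powerful in every setting tried. Neither the sample size nor the stated 80% is shown to be wrong. This is a recommended clarification with a gain in precision, not a defect that invalidates the design.

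**What to change.** State in Statistical analyses that the primary ICS analysis is the model assumed in Sample size: random intercept and slope, the treatment-period segment of the piecewise time function, and arm by time. Give the arms a common baseline mean, or enter baseline ICS as a covariate. Write the single primary test as one parameter: the arm difference at post-test. Confine data-driven model building to secondary outcomes and follow-up description.

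The cost is analysis wording only, with no change to data collection, participants or sample size.

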### Outcome measures and data collection

See table 2 for a list of measures and when they will be collected. All outcomes will be self-reported via the internet. The primary outcome concerns gambling behaviour and consequences for the IP and their CSO. This will be measured by the Inventory of Consequences Scale for the Gambler and CSO (ICS).^45^ The scale was adopted from the substance abuse field and consists of three subscales: (1) consequences for the gambler, (2) negative emotional consequences for the CSO and (3) negative behavioural consequences for the CSO. It was used in a similar study with CSOs of people who gamble.^20^ Internal consistency was good, ranging from α=0.86 to 0.89 for the different subdomains. Test-retest reliability was excellent over 7 to 10 days (ICC=0.93 for all domains).^45^ Although lacking an extensive psychometric evaluation, these results indicate good psychometric properties in a relevant sample. Gambling behaviour will be reported by the CSO, and will be measured by the timeline followback method for the past 30 days, and continuously during the study. CSOs will be asked to report days gambling and money spent. Previous studies have found fair agreement between reports from CSOs and the IP,^45^ indicating that the CSO's report of gambling behaviour is reasonably valid and reliable as a proxy measure of problem gambling behaviour. CSOs will also be asked to report whether and when the IP decided to enter treatment. Treatment engagement is defined as completing at least one treatment session or agreeing to call the National Gambling Helpline. We choose to include calls to the Helpline since they work with MI, and research has shown that such brief interventions can reduce gambling problems.^46^

**Table 2 BMJOPEN2015008724TB2:** Outcomes and their placement during the study

Outcome	Measure	Pretest	Weekly during treatment*	Post-test, 6, 12 months
Primary outcome				
Gambling consequences	ICS	X	X	X
Secondary outcomes				
Treatment engagement	–	X	X	X
Gambling behaviour	TLFB: days, money	X	X	X
Depression	PHQ-9	X	X	X
Anxiety	GAD-7	X	X	X
Relationship	RAS	X	X	X
Quality of life	WHOQOL-Bref	X		X

*Not all measures are answered by all participants every week; see the section about ‘planned missingness design’.

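### The timeline-followback analysis treats money spent as a count: zero-inflated Poisson or negative binomial results depend on the currency unit and can be anti-conservative

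*Protocol article*

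**What the plan says.** Under Outcome measures and data collection, the followback has two components: "CSOs will be asked to report days gambling and money spent". Table 2 lists it among the secondary outcomes as "TLFB: days, money". Gambling behaviour "will be measured by the timeline followback method for the past 30 days, and continuously during the study". The note to Table 3 (Planned missingness design) gives the weekly window as "TLFB (last 7 days".

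The Statistical analyses section then deals with both components in one sentence: "for the analysis of the timeline followback reports (count data), it is anticipated that the data will be positively skewed and bounded at zero". The model follows: "Hence, generalised linear mixed models will be fitted, specifically zero-inflated Poisson models". So does the fallback: "In the case of overdispersion, zero-inflated negative binomial regression models will be fit".

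The same section also states: "Continuous outcomes will be analysed using a linear mixed models approach". Nothing there or elsewhere links that sentence to money spent, and no other model is named for money. The upper limit on days is not mentioned.

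**The concern.** The count label is attached to the followback reports as a whole, yet one of the two variables is an amount of currency. Poisson ties the variance to the mean, and for an amount that tie has no meaning: recording the same spending in single kronor, hundreds or thousands changes the standard error and hence the p-value. The negative binomial loosens the tie, but it is still a distribution on integers and its variance is a set function of the mean.

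At stake is the third hypothesis, that the programme reduces the time and money the gambler spends on gambling. For money, the risk is a false positive or a conclusion that depends on an arbitrary unit.

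A smaller issue concerns days. They cannot exceed 7 or 30, but the section recognises only the bound at zero, and the fallback addresses overdispersion alone.

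**Working it through.** The protocol states no figure for this analysis, so there is none to reproduce. From the document come 1:1 allocation, 75 per group, α = 0.05 (taken as two-sided) and the 7- and 30-day windows. Every property of the spending and gambling data below is an assumption.

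**1. Money, Poisson step: why the unit matters.** Assume 30% zeros and log-normal positive amounts with median 2000 and log-SD 1.2.

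- Spenders per arm: 75 × 0.70 = 52.5.
- Mean positive amount: 2000 × exp(1.2²/2) = 4109.
- Poisson SE of the log ratio of means in unit u: √[2 / (52.5 × 4109/u)]. This gives 0.0030, 0.030 and 0.096 for u = 1, 100 and 1000.
- Actual SD of the log ratio of means: squared coefficient of variation exp(1.44) − 1 = 3.22, so √(2 × 3.22/52.5) ≈ 0.35, whatever the unit.

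Simulated zero-inflated Poisson fits agree:

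| Unit | Mean model SE | Empirical SD | Ratio | Type I error |
|---|---|---|---|---|
| 1 | 0.0031 | 0.320 | 0.01 | 99.5% |
| 100 | 0.0312 | 0.325 | 0.10 | 83% |
| 1000 | 0.1031 | 0.344 | 0.30 | 60% |

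A separate null simulation of the Poisson part gave 98%, 85% and 45%.

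**2. Money, after the fallback.** A variance this far above the mean would trigger the negative binomial. On the same data its SE ratio was 0.70 in unit 1 and 0.69 in unit 100, with type I error 17.5% and 17%. As a check, 2[1 − Φ(1.96 × 0.70)] = 0.17. In unit 1000 only 33 of 200 fits were usable, so that result is set aside.

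With 25% zeros, median 1500 and log-SD 1.2, the fallback rejected in 20%, 16% and 11% of null trials in units of 1, 100 and 1000. Between units of 1 and 1000, 9% of trials changed verdict. A further run at log-SD 1.2 gave 18%, 17% and 12%.

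**3. Money, dependence on the tail.** Fallback type I error across the simulations:

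| Assumed positive amounts | Type I error |
|---|---|
| Log-normal, log-SD 0.5 | 4–8% |
| Log-normal, log-SD 0.8 | 6–13% |
| Log-normal, log-SD 1.2 | 11–20% |
| Gamma, shape 0.7, 1.0, 1.5 | 5%, 9%, 5% |

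A log-normal model for the amounts gave about 5% on the log-normal data. Gamma regression with model-based errors gave 22% at log-SD 1.2 and 12% at 0.8, against 18% and 13% for the fallback in the same runs. The choice of standard error therefore matters as much as the choice of distribution.

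**4. Days.** If every person gambles on each day with the same probability p, the variance is (1 − p) times the mean, so the Poisson SE is too large by 1/√(1 − p).

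| p | SE too large by | Poisson probability above 7 |
|---|---|---|
| 0.2 | 1.12 | 0.0% |
| 0.4 | 1.29 | 0.8% |
| 0.6 | 1.58 | 6.4% |
| 0.7 | 1.83 | 12.3% |

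Simulated with 30% structural zeros, the zero-inflated Poisson SE ratio was 1.05 to 1.62 for homogeneous people. With a between-person correlation of 0.3 it was 0.84 and 1.02 on the 7-day window, and 0.43 and 0.52 on the 30-day window. On the overdispersed 30-day counts the fallback restored ratios of 1.03 and 1.15 (type I error 4.7% and 2.7%). On underdispersed days it could not be estimated reliably.

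**The case against.** The strongest reply is that the plan contains its own remedy. A reader might infer from the Poisson figures that nearly every null trial would be declared positive for money. The document does not support that, because the overdispersion rule would replace the Poisson fit before reporting. This stands: the Poisson figures show only why the first model has no meaning for money.

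Second, the remaining inflation depends on the assumed tail and largely disappears for gamma amounts or a small log-SD. The simulations also use one time point and no random effects, while the plan specifies mixed models for repeated data. Random effects may absorb part of the between-person spread. This also stands, so the percentages are illustrations, not the error rate of the planned model.

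Third, the count label may have been meant for days only, and a condensed article may leave the model for money to an analysis plan. But the sentence names the followback reports without restriction, after the article has defined them as days and money. The issue is the scope of a stated rule, not a missing detail.

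Fourth, for days the anticipated positive skew suggests low gambling frequencies, where the cap hardly matters, and standard errors that are too large are conservative. This largely stands. A reader might also infer that 7- and 30-day reports will be pooled on one scale. The text does not say so, and an offset would deal with it.

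**Conclusion.** The concern holds for money. As written, the rule applies a count likelihood to a semicontinuous amount. Inference on money would depend on the currency unit and could be anti-conservative after the fallback. Under the stated assumptions the size ranges from about nominal (gamma amounts, or log-SD 0.5) to 11–20% type I error at log-SD 1.2. The document gives no spending distribution with which to narrow that range.

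For days the point is secondary. Poisson errors may be too large when gambling is frequent and people are alike, too small when people differ, or about right. The fallback can correct overdispersion but not underdispersion. It would go too far to conclude that the standard errors for all followback data will be wrong.

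The consequence is confined to the secondary outcome behind hypothesis 3. The ICS analysis, the treatment-entry analysis and the sample size are unaffected.

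**What to change.** Restrict the count-model sentence to gambling days. For money, specify a two-part mixed model: logistic for any spending, and log-normal for the amount given some spending, with robust or bootstrap standard errors. If a gamma model is used for the amount instead, robust or bootstrap errors are essential, since its model-based errors did no better than the negative binomial on heavy-tailed data.

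For days, preferably use a binomial or beta-binomial mixed model with the number of days covered (7 or 30) as denominator, zero-inflated if needed. This respects the cap and puts both windows on one scale.

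The cost is a few sentences of analysis wording, settled before unblinded analysis, and standard software. No new data are needed.
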